#### Objective #2

Participants (i.e., parents, co-parents, community health and social service agency administrators and health and social service providers) must be adults (18 years of age or older), and English speaking and reading, and knowledgeable or experienced in parenting programs.

### Intervention {11a, 11c and 11d}

ATTACH^TM^ intervention sessions include three components:Parent-child interactions are videotaped during 3–5 minutes of free-play for review and discussion. During the video feedback, the ATTACH^TM^ facilitator explores the parents’ perceptions of themselves and their children, and maximizes opportunities to practice RF (e.g., parents are asked to consider what may be happening with her thoughts and feelings and with her child’s thoughts and feelings during a shared smile in the videotaped interaction).A hypothetical, mildly stressful situation is discussed. Hypothetical situations encourage imagining others’ thoughts and feelings in a common daily life, such as during dinner when the child throws food on the floor.Day-to-day real-life stressful situations are discussed. Real-life stressful situation reviews revolve around parents’ and others’ thoughts and feelings as the stressful situation is described in detail. When co-parents are present, only the free-play videotaped interactions and hypothetical situations are examined. To avoid any potential conflict, real-life stressful situations are excluded from co-parent sessions.

Throughout, ATTACH^TM^ interventionists bolster parents’ RF through questioning and maintaining a curious stance about parents’, children’s and others’ thoughts and feelings. Once the therapeutic relationship is established (after approximately 6 one-on-one sessions of therapy), parents invite their co-parenting support person (e.g., father, mother, relatives, friends, or other support person) to 2 sessions, typically at sessions 7 and 9, spaced 2 weeks apart. At least 2 interventionists will be trained in ATTACH^TM^ at each agency using online modules and in-person practice that takes a total of 20 hours.

### Outcomes {12}

Parent-Child Relationship Quality will be measured with the Parent-Child Interaction Teaching Scale (PCITS) [81]. The PCITS is an observational binary measure of relationship quality in an everyday teaching situation, designed for children 36 months or younger. It is considered the gold standard for the assessment of parent-child relationship quality. The PCITS consists of 73 items categorized into six subscales including parental sensitivity to cues, responsiveness to distress, growth fostering, and cognitive growth fostering, child clarity of cues and responsiveness to parent as well as parent total, child total, and parent-child total scores. The scales’ reliability and validity are well established and was observed to be a strong measure of intervention impact in our pilot studies . The observation typically takes 5 minutes to administer and is videotaped to enhance the accuracy of data coding. ATTACH^TM^ interventionists who are health and social service providers in agencies, will be trained to administer the videotaping. Colleagues from the University of Washington will code all videos. During the pilot studies, they retained > 95% intra-rater reliability on 10% of recoded videos and reliable at the 90th percentile with the Canadian study team. Coders are supervised by PI [name] who has been a certified PCITS trainer since 1996 and has kept up annual certification. A protocol for data collection was developed as part of the pilot studies and discussions with patients revealed that the assessment is feasible and acceptable.

#### Secondary outcomes. Reflective function (RF)

Two measures of RF will be employed, one to assess general RF and the other to assess parental RF. General RF is distinct from parental RF as the concept of parental RF is more parent–child relationship-specific [82]. The Parental Reflective Function Questionnaire (PRFQ) [80] is an 18-item measure of parental RF, with subscales assessing (1) certainty about mental states and (2) interest and curiosity about mental states. Higher scores indicate higher levels of RF. The PRFQ has good internal consistency (.7–.84) and takes 5 minutes to complete refs. The Reflective Functioning Questionnaire (RFQ) [83] is an 8-item measure of RF that provides a total score for RF. Created by Peter Fonagy, the measure has acceptable reliability and validity and takes less than 5 minutes to complete. Pilot testing revealed the PRFQ and RFQ each detected intervention impacts and were acceptable to patients. In our other work [82], we showed that scores on the RFQ and PRFQ were significantly associated with the gold standard Parental Development Interview coded with Fonagy’s 11-point scale. Given the gold standard requires 1–2 hours per patient interview, 3–4 hours for transcription, followed by 2 hours coding per interview, the use of the RFQ and PRFQ significantly reduces both patient burden and cost of administration and are feasible to implement in agencies.

We will employ the Ages and Stages Questionnaire-3rd Edition (ASQ-3) [84] to assess child development in cognitive and motor domains. The cognitive measures include communication, problem solving, and personal-social skills development, while motor measures include both gross and fine motor development. The ASQ-3 is a series of parent-completed questionnaires for age groups ranging from 1 to 66 months, asking six questions in each domain assessing children’s abilities to undertake age-appropriate tasks. Summing items in each domain provides total scores (maximum 60) with higher scores indicating more optimal development; cut-offs are provided to indicate risk for developmental delay in each domain, appropriate to each age group. The ASQ-3 is typically administered in community agencies, thus both agencies and our pilot patients found this measure acceptable and feasible. The ASQ-3 is found to have strong internal consistency reliability (between 0.82–0.88), sensitivity of 86% and a specificity of 85% [85] and is used to identify children at risk for developmental disorder [86].

Dried blood spots (DBS) for assessment of immune biomarkers will be collected by either ATTACH^TM^ interventionists/agency health and social service providers or the research team (agency preference), pre- and post-assessment (only; no 3 month delayed post-intervention assessment), to assay children’s immune cell gene expression (mRNA) [87] and epigenetics (DNA methylation) [88]. DBS collection protocols to reduce distress/discomfort of children were pilot tested with 20 families. While the DBS pilot was optional and parents’ choice, *all children* (*n* = 20) provided blood samples pre- and post-assessment, with minimal distress in children or concerns expressed by parents. Our consultation with agency partners dictates that the DBS will remain optional to avoid deterring patients from participating in ATTACH^TM^. However, our high pilot uptake rate (100%) suggests we will have a sufficient sample. Briefly, a finger is pricked and drops of blood are collected onto specially prepared filter paper cards.

DBS collection is less invasive than traditional venipuncture techniques and is specifically designed for field use [89]. Sex and gender based analysis will also be conducted [90].

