### Trial design {8}

This EIH type 2 [29] study is a quasi- experimental evaluation of the ATTACH^TM^ program and implementation feasibility [75, 76]. **Objective 1: ATTACH**^**TM**^
**Impacts**, will be addressed via a quasi-experimental design to closely approximate service delivery models in agencies that do not typically employ control groups. Moreover, a RCT design, even employing wait-list controls was deemed unacceptable and even unethical by parents, health and social service providers, and health system administrators in engagement activities surrounding the preparation of this proposal. **Objective 2: ATTACH**^**TM**^
**Implementation Feasibility,** will be addressed via Normalization Process Theory (NPT) to understand factors that promote or inhibit interventions from being embedded in practice [75–77]. Developed in response to recognition of the large gap between intervention development and intervention use in health care—the ‘know-do gap’—, NPT is intended to uncover factors that interfere with the routine or “normal” incorporation of interventions into health care [78]. NPT will guide qualitative semi-structured interviews and analysis exploring patients’, health and social service providers’, and health system administrators’ perceptions and experiences of the benefits, facilitators, barriers, and challenges to ATTACH^TM^ implementation in community agencies.

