##### Quantitative component

We will recruit until we have completed all study components with 100 new families, a sufficient *n* to detect minimum *d* = .34 for pre- /post- assessment differences in parent-child relationship quality. From discussions with agency health and social service providers and administrators, it will be feasible to recruit 30 families (including parents, co-parents, and children) from each agency, from patients currently seeking service, to retain 20 of them for 3 months postintervention for follow-up (any longer was deemed unrealistic given potential for patient relocation). Specifically, iKT and end-of-grant dissemination will be planned in partnership with agency health and social service providers and administrators.

#### Objective 2

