### Statistical methods {20a, 20b and 20c}

We will analyze the demographic characteristics of the sample with measures of central tendency and frequencies as appropriate. For all analyses, alpha will be set a priori at .05 (two-tailed).

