#### Objective 1: ATTACH^TM^ impacts

For (1a), Evaluate ATTACH^TM^ impacts on parent-child relationship quality (primary outcome), parental RF, and child development and (1d) evaluate long-term impact of ATTACH^TM^ (3 months delayed post-assessment), we will employ repeated measures analysis of variance (ANOVA), paired-t-tests, and chi-square tests to examine outcomes between pre-assessments, post-assessments and at 3 months post-assessment follow-up. For (1b) Determine whether ATTACH^TM^ is equally effective across patient populations (and for whom it works best/worst), we will examine differences among sub-groups derived from known covariates through use of independent samples *t*-tests (two groups, e.g., child sex), ANOVAs (more than 2 groups, e.g., race/ethnicity), repeated measures analysis of covariance (with identified covariate) and linear regression models (continuous covariate, e.g., age, years of education). For (1c) evaluate whether ATTACH^TM^ impacts immune biomarkers indicative of inflammatory disease risk, (i.e., gene expression, DNA methylation).

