### Confidentiality {27}

To protect confidentiality and anonymity of findings, all data will be held in confidence, numerically coded with identifying information removed, and stored on a secure network drive. No personal email addresses or accounts will be used for communication purposes or for data sharing. The staff will ensure that the participant signs the consent form to understand the privacy and confidentiality nature of the study in the beginning. Additional steps may include reiterating the privacy and confidentiality nature of the study before digital video-recording taping.

Parents’ demographic information including name and age will be collected by the partner agencies. With the exception of the consent form (stored separately), only de-identified data will be shared with the ATTACH^TM^ team. The demographic information will be used to describe our sample in future publications. Interactions between the parents and children will be digitally video recorded to assess parent child interaction quality. These assessments are age specific. Any video digital data will be password protected or encrypted. The researchers will not have access to identifying information as participants will only be identified with an ID number. Any identifying information will be removed from the beginning and replaced with an ID number for analysis. Only the research team will have access to questionnaire response data. All information provided by participants will be kept confidential, except when it needs to be reported as required by law (when participants express a desire to do harm to themselves or others). No participant will be identified in any publications or presentations that come from this research. The findings of this study will be reported as aggregate data at health conferences and in journal publications; however, any information that could identify the participants will not be included.

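### Objectives 1a and 1d test visit-to-visit change in growing children with no allowance for child age, so ageing cannot be separated from programme effect on the ASQ-3 and the child-dependent PCITS scores

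*Protocol article*

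**What the plan says.** **Design.** Trial design {8} gives objective 1 "a quasi-experimental design to closely approximate service delivery models in agencies that do not typically employ control groups". It adds that even a wait-list control was judged unacceptable. There is one group, measured before, after and three months after the programme.

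**Age and timing.** Eligibility criteria {10} admits children from birth to 32 months and describes ten weekly sessions. Participant timeline {13} has sessions usually starting the week after pre-assessment, and the delayed visit three months after post-assessment.

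**Outcomes.** Outcomes {12} describes the PCITS as having four parent subscales and two child subscales (clarity of cues, responsiveness to the parent), with parent, child and parent-child totals. The ASQ-3 is a series of questionnaires for different age groups, asking about tasks suited to the child's age: "Summing items in each domain provides total scores (maximum 60) with higher scores indicating more optimal development". The same paragraph says that every domain has thresholds for risk of delay, and that these differ by age.

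**Analysis.** For 1a (impact) and 1d (long-term impact), Statistical methods {20a, 20b and 20c} says "we will employ repeated measures analysis of variance (ANOVA), paired-t-tests". The sentence goes on to chi-square tests and the three assessment times. Age appears only under 1b, as an example of a continuous covariate for subgroup differences. Data collection methods {18a, 18b} lists child age among the items obtained at pre-assessment.

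**The concern.** Without a comparison group, the visit effect is the sum of everything that changes between visits. In children this young, one of those things is age. The tests named for 1a and 1d do not remove it, and naming age under 1b does not help, because a subgroup covariate leaves the mean time contrast as it was. Even baseline age added as a covariate would leave the average change unadjusted.

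Two outcomes depend on the child:

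- **PCITS child and parent-child totals.** These include items on the child's behaviour. If such scores move with age, the pre/post difference contains that movement. The PCITS measures the primary outcome.
- **ASQ-3 domains.** A child who moves to an older age group answers a different questionnaire. Two sums out of 60 from different questionnaires are then subtracted or put into one ANOVA, and nothing in the protocol shows that they share a scale.

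At stake is the meaning of a significant result under an objective worded as impact. The delayed visit is the more exposed, because the children have aged more than twice as much.

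**Working it through.** **1. Intervals.** Ten weekly sessions plus about one week before the start is 11 weeks. 11 / (52.18/12) = 2.5 months to post-assessment. Adding 3 months gives 5.5 months to the delayed visit.

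**2. The plan's own figure.** Sample size {14} calls 100 families "a sufficient *n* to detect minimum *d* = .34 for pre- /post- assessment differences in parent-child relationship quality" and states no power. A paired t-test with n = 100, two-sided alpha .05 and d = .34 (mean change / SD of change) has power .92 from the noncentral t. The size is sufficient for that effect. By the same function, a drift of modest size is also enough for significance.

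**3. Drift from ageing alone.** Assumptions, none given in the protocol:

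- entry ages uniform over 0 to 32 months, so age SD = 32/√12 = 9.24 months;
- score linear in age, with correlation r at entry;
- pre/post correlation .5, so SD of change = √(2(1 − .5)) = 1 score SD;
- no programme effect, n = 100.

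Drift = r × months / 9.24. Rejection is the two-sided noncentral t probability with noncentrality drift × √100.

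| r | Drift, post | Rejects, post | Drift, delayed | Rejects, delayed |
|---|---|---|---|---|
| 0 | 0 | 5% | 0 | 5% |
| .05 | .014 | 5% | .030 | 6% |
| .1 | .027 | 6% | .060 | 9% |
| .3 | .081 | 13% | .179 | 42% |
| .5 | .135 | 27% | .298 | 84% |

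At r = .5 the drift is .135/.34 = 40% of the planning effect at post and .298/.34 = 88% at the delayed visit. The table illustrates a score on one scale with a smooth age trend, such as a PCITS child score might have. It does not describe ASQ-3 sums taken from different questionnaires.

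**4. ASQ-3 change of form.** The widths of the age groups are not given. For an assumed width w, the share of children changing form is about min(1, interval/w):

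| w (months) | Pre to post | Pre to delayed |
|---|---|---|
| 2 | 100% | 100% |
| 3 | 83% | 100% |
| 6 | 42% | 92% |

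**5. Precision cost of an age adjustment.** If the age slope is estimated at pre-assessment, the correction has standard error months × √(1 − r²) / (9.24 × √100). The unadjusted standard error is 1/√100 = .100. At r = .3:

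- post: correction .026, total √(.100² + .026²) = .103, or 3% wider;
- delayed: correction .057, total √(.100² + .057²) = .115, or 15% wider.

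Over r = 0 to .5 the widening is 3 to 4% at post and 13 to 16% at the delayed visit.

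**The case against.** **Age-matched forms already remove some development.** This stands. An older ASQ-3 form sets tasks suited to the older child. A reader might infer that ordinary development is simply counted as programme gain on the ASQ-3. The documents do not support that: the shift between forms may raise or lower the sum. What remains is the lack of a shown common scale.

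**Chi-square may be meant for cut-off status.** It may. Cut-off status is the only ASQ-3 category described, and it is age-referenced. But the text does not say which score goes into which test, and it offers ANOVA and paired t-tests for the same outcomes.

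**The protocol acknowledges age-specificity.** Confidentiality {27} says "These assessments are age specific". This follows a sentence on videotaped parent-child interaction, so it concerns the PCITS and not the ASQ-3 forms. No age-referenced PCITS score is described anywhere.

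**PCITS drift is unproven and the correlations are invented.** Both are true. Nothing in the protocol says that PCITS scores rise with age, and most of its subscales describe the parent. At r near 0 the test keeps its 5%. The calculation shows what could happen, not what will.

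**The design is disclosed.** Lack of a control group is openly justified and is not itself an error. The fault is an analysis and wording of impact that make no use of the age information at hand.

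**Parental reflective function.** A reader might extend the point to the PRFQ and RFQ. These are adult questionnaires, and the documents state no mechanism by which the child's ageing would move them.

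**Conclusion.** The point holds for child-dependent outcomes. As written, 1a and 1d confound ageing with programme effect for the ASQ-3 domains and for PCITS scores that include child items. For the ASQ-3 they also leave open a comparison of sums from different questionnaires, with bias in an unknown direction and an unknown share of children changing form.

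The size cannot be fixed from the documents. Under the assumptions above, false rejection ranges from the nominal 5% to 27% at post-assessment and from 5% to 84% at the delayed visit. These ranges rest on the assumed correlations of 0 to .5, uniform entry ages and a pre/post correlation of .5. They do not show that a significant result would be spurious. They show that the planned tests could not tell.

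**What to change.** In Statistical methods {20a, 20b and 20c}, for 1a and 1d:

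1. **ASQ-3.** Analyse each domain relative to its age-specific reference or cut-off at each visit, not as a sum out of 60. Say which test applies to which score.
2. **PCITS scores with child items.** Add a repeated-measures model with child age at each assessment (linear or spline) plus visit. The wide entry-age range identifies the age trend, and the visit effect is change beyond it. State two limits: the model assumes that age differences between children match growth within a child, and it extrapolates slightly, since a child entering at 32 months is 34.5 and 37.5 months old at the later visits.
3. **Wording.** Report 1a and 1d as pre/post change, or as change beyond age expectation where adjusted. Do not present it as impact attributable solely to ATTACH. Study setting {9} says the programme is added to existing agency services, which run alongside it.

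Cost: some extra analysis, and confidence intervals for the adjusted scores about 3 to 4% wider at post and 13 to 16% wider at the delayed visit. Child age is already collected at pre-assessment, and age at later visits follows from the visit dates. No new visits or families are needed.

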#### Objective 2: ATTACH^TM^ implementation feasibility

Using NPT in implementing complex interventions requires the developing an interview guide to address four key concepts: coherence, cognitive participation, collective action, and reflexive monitoring of the intervention [78]. In finalizing the interview guide and developing the interview processes (e.g., home or clinic setting, telephone/skype, or in-person), Patient Engagement Committee (PEC) and Community Engagement Committee (CEC) members will review, provide feedback, and make decisions about interview guide content. The interview guide will be pilot tested before use. Interviews will be audio-recorded and transcribed verbatim with appropriate privacy protections in place to guard participant identity and personal information, followed by conducting qualitative thematic analysis [91].

### Participant timeline {13}

#### Objective 1

##### Pre-assessment

The ATTACH^TM^ program begins with administering pre-assessment data collection. This is essential to evaluate the ongoing effectiveness of ATTACH^TM^. The participants will be asked to provide observational, questionnaire, and biological data.

##### ATTACH^TM^ reflective function intervention

The ATTACH^TM^ Reflective Function Intervention can begin after the pre-assessment sessions are completed–usually the following week. ATTACH^TM^ intervention sessions include three components, described above in {11}:

##### Post-assessment phase

The ATTACH^TM^ intervention must be complete before post-assessment which includes parents’ providing observational, and questionnaire data. Dried blood spots (DBS) will be collected by either ATTACH^TM^ interventionists/ agency health care professionals or the research team (agency preference), pre- and post-assessment (only; no 3-month delayed post-assessment), to assay children’s immune cell gene expression (mRNA) and epigenetics (DNA methylation).

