##### **ATTACH**^TM^**impacts**

Every partner agency (including additional agencies) will recruit 2–5 staff members for ATTACH^TM^ training to become the ATTACH^TM^ facilitators. To partake in the ATTACH^TM^ parenting program, participants will be identified through partner agencies. We will intervene with up to 150 parents and their birth to 36-month-old children to retain 100, from 5 community agencies. Parents will be recruited from rosters of patients currently seeking service. The ATTACH^TM^ information sheets and brochures will be posted on implementation sites. Their current and interested clients will be our potential participants. Their staff will assist with recruitment as participants seek their services in routine care.

#### Objective 2

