The voluntary nature of the study will be reinforced verbally throughout the consent process and, indeed, throughout the course of the participant’s involvement in the study. They may choose not to answer some questions asked or to withdraw from the study at any time without affecting their health care or participation in partner agencies’ services. If they choose to no longer participate (at any time including once data analysis has begun), we will retain their data for attrition analyses, unless asked explicitly to remove data from the study, in which case their data collected to date will be destroyed. The interested agencies will approach the potential ATTACH^TM^ participants who are already accessing services at the agencies. Staff at the participating agencies will ensure to avoid any coercion by letting the potentially interested families know that their participation is completely voluntary, and that they can withdraw any time. It will not affect their access to any other services at the agencies if they decide to not participate in the study. To protect the rights of participants, this study will meet the ethical standards set out in the Conjoint Health Research Ethics Board Guidelines refs. A process of informed consent will be implemented, with verbal consent being secured at each stage of the process. In addition to the verbal consent secured during the recruitment and screening process, participants will be provided with a written consent form and will be required to return a signed copy of the written consent form.

We also received ethical approval for an adaptive honorarium schedule of gift cards that provides increased compensation commensurate with increased parent burden. This schedule emerged from numerous collaborative conversations with parents and agency health and social service administrators and providers. The study participants will receive $280 honorarium in total to appreciate them for their time. Additional $100 ($50 × 2 per sampling) will be offered to the families for dried blood sampling collection in the first 80 families in Calgary agencies. Participating agencies will cover the cost for parking and travel, as their typical practice.

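### The effectiveness sample is defined by completion and no outcome is described for families who stop early, so the uncontrolled pre/post change carries selection bias of unknown size and sign

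*Protocol article*

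**What the plan says.** Five places in the protocol article bear on who contributes to the effect estimate.

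- **Sample size {14}:** the target is a count of finishers: "We will recruit until we have completed all study components with 100 new families". The same sentence calls this "a sufficient *n* to detect minimum *d* = .34 for pre- /post- assessment differences". The section expects each agency to recruit 30 families and keep 20 of them to 3 months after the intervention.
- **Recruitment {15}:** "We will intervene with up to 150 parents and their birth to 36-month-old children to retain 100, from 5 community agencies".
- **Participant timeline {13}, Post-assessment phase:** "The ATTACH^TM^ intervention must be complete before post-assessment". No assessment is described for a family that stops before the end.
- **Research ethics approval and consent {24 and 26a}:** for people who stop participating, "we will retain their data for attrition analyses", unless they ask for removal. No other use is named.
- **Statistical methods {20}, Objective 1:** for the primary outcome and the 3-month question, "we will employ repeated measures analysis of variance (ANOVA), paired-t-tests" and chi-square tests, all at two-sided .05.

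Trial design {8} states that there is no control group. No section names all starters as an analysis set or provides for assessing families who leave the program.

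**The concern.** Objective 1 asks whether the program works when ordinary agency staff deliver it to the families they serve. That is a question about families who start. The design as written measures families who finish.

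In a controlled trial, selective loss is at least partly visible as a difference between arms. Here the estimate is a single mean change. If families who are gaining tend to stay and those who are not tend to leave, the completers' mean exceeds the starters' mean, and nothing in the data shows how much of it is selection. Enrolling beyond 100 to end with 100 finishers restores precision but does not touch this bias.

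Much of the problem lies in data collection rather than analysis. A post-assessment that was never sought cannot be recovered by an analysis plan written later.

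**Working it through.** **Inputs from the protocol.** 100 completers and up to 150 starters (Sample size {14}, Recruitment {15}); 30 recruited and 20 kept per agency to 3 months (Sample size {14}); d = .34; two-sided alpha .05.

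**My assumptions.** d is in units of the SD of the change, since the standardiser is not stated. The leavers' mean change, the correlation r between change and propensity to finish, and the loss before post-assessment are not given, so each is shown over a range.

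**1. The plan's own figures.** Loss = 1 − 100/150 = 33.3%, and 1 − 20/30 = 33.3%. Inflation: 100/(1 − 1/3) = 150. Five agencies give 5 × 30 = 150 and 5 × 20 = 100. (Study setting {9} lists four initial agencies, which would give 120 and 80; that count needs reconciling separately.) For a paired t-test with n = 100 and d = .34, the noncentrality is .34 × √100 = 3.4 and power is 92%. No power is stated, but 80% needs 70 families and 90% needs 93. On this reading 100 is enough for precision.

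**2. Completers against all starters.** If completers change by .34 and one third of starters leave, the all-starter mean is (100 × .34 + 50 × leavers' change)/150.

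| Leavers' mean change | All-starter mean | Completers minus all starters |
|---|---|---|
| −.34 | .113 | +.227 |
| 0 | .227 | +.113 |
| .17 | .283 | +.057 |
| .34 | .340 | 0 |
| .50 | .393 | −.053 |

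**3. False-positive rate when the true mean change is zero.** Let propensity to finish be standard normal, with the lowest fraction q leaving. The mean propensity among those who stay is φ(z_q)/(1 − q), and the spurious standardised change is r times that.

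- q = 1/3: z = −0.431, and 0.3636/0.6667 = 0.545.
- q = 1/6 (half the stated loss falling before post-assessment): z = −0.967, and 0.2499/0.8333 = 0.300.

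The rejection rate is from the noncentral t with 99 df and noncentrality 10 × shift (n = 100).

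| r | Shift, q = 1/3 | Rejects | Shift, q = 1/6 | Rejects |
|---|---|---|---|---|
| 0 | 0 | 5% | 0 | 5% |
| 0.1 | 0.055 | 8% | 0.030 | 6% |
| 0.2 | 0.109 | 19% | 0.060 | 9% |
| 0.3 | 0.164 | 37% | 0.090 | 14% |

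A negative r gives shifts of the same size in the opposite direction.

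**4. Which tests lose which families.** A standard repeated-measures ANOVA over three visits drops a family with pre and post data but no 3-month visit. A pre/post paired t-test keeps that family. Both drop a family with no post-assessment.

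**5. Would a change of model suffice?** I simulated two-visit data under the selection model in step 3 (one-third loss, r = 0.2 and 0.3, pre/post correlation 0.3 to 0.7) and used leavers' baselines in a likelihood estimate. About 66% to 86% of the bias remained, because leaving depends on a change that is not observed.

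**The case against.** The strongest reply is that analysis sets and missing-data methods usually belong in an analysis plan or full protocol, neither of which is shown. That would answer a complaint about silence. It does not answer a recruitment target defined by completion, which this text fixes, or the lack of any described assessment of early leavers.

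Several narrower objections stand and limit the point:

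- A reader might infer that the effect is certainly biased upward. The documents do not support that. No leaver outcomes are reported, and the one cause of loss named is relocation, given as the reason against longer follow-up. If leaving is unrelated to change, r is near zero and there is no bias.
- A reader might apply the full one-third loss to the primary pre/post contrast. The per-agency figure runs to 3 months after the intervention, so loss before post-assessment may be smaller. The full third applies only if analysis is confined to families with every component.
- A reader might say the protocol restricts leavers' data to attrition analyses. The consent section names that use without calling it exclusive, and it concerns people who withdraw, not those who merely miss sessions.
- The post-assessment sentence can be read as sequencing, so the sample-size sentence is the firmer anchor.
- The protocol describes capped over-enrolment; it does not speak of replacing dropouts.

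**Conclusion.** The point holds in this form: the protocol defines its effectiveness sample by completion, describes the outcome visit only after a finished program, and gives leavers' data no stated role in the effect estimate. With no control arm, selection bias enters the mean pre/post change directly and cannot be distinguished from benefit.

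Its size and sign are unknown; upward is plausible. Over the assumed range r = 0 to 0.3, the spurious change is 0 to 0.16 SD at one-third loss and 0 to 0.09 SD at one-sixth loss. If completers change by .34 and one third of starters leave with no change, the effect among starters is .23; if leavers change equally, there is no bias. These are illustrations resting on the assumed correlation, loss and leaver change, not estimates for this trial.

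**What to change.** 1. Seek the PCITS post-assessment, in a set window after pre-assessment, from every family that starts and still agrees to be assessed, whatever its attendance. This is the essential part; step 5 shows that modelling alone leaves most of the bias under the assumed selection model.
2. Make the primary analysis set all families with a pre-assessment. Replace the three-visit ANOVA with a likelihood-based mixed model that uses every available visit.
3. Reword the consent section {24 and 26a} so that retained data enter the effectiveness analysis unless removal is requested.
4. Report the completer result as a sensitivity analysis.

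**Cost.** Up to about 50 further standard assessments, each with video and external coding; an amendment to the post-assessment and data-use wording; and a headline estimate that may be smaller. There is some return in precision: if the all-starter change were .227, a paired test on 150 assessed families would have 79% power, against 61% with 100. Recruitment is already under way (Status of trial), and a leaver whose outcome is not sought at the time is unlikely to be recoverable, so the change should be made soon.
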